#### 7.6.4 ELECTROCARDIOGRAM

A 12-lead ECG will be performed during the screening visit and in week 36. During an ECG, it is advised that the test subjects are in a quiet environment without distraction (e.g. television, cell phones) and lie in a supine position. The patient should rest for at least 5 minutes before the ECG recording and should not speak or move their arms or legs. If an abnormal result is recorded, the ECG should be repeated.

#### 7.6.5 VITAL SIGNS

The following vital signs will be obtained at every visit:

- blood pressure
- weight
- temperature
- pulse/heart rate

#### 7.6.6 PHYSICAL EXAMINATION

At the screening visit, a complete physical full body examination will be performed. A full physical examination includes assessment of the general appearance, the head (including oral cavity and teeth), ears, nose, the eyes, throat, neck, abdomen, lymph nodes and peripheral extremities, as well as the hear, respiration, neurology, musculoskeletal system, skin, urogenital area (if clinical signs are present).

A targeted physical examination will be performed at each other visit and before treatment, as shown in the flow chart in Chapter 7.1.1. A targeted physical examination includes assessment of the general appearance, head (including oral cavity and teeth), eyes, nose, throat, abdomen, lymph nodes and the

following systems: cardiovascular system (including peripheral vessels), respiration, neurology, musculoskeletal system and skin.

#### 7.6.7 PREGNANCY

Female patients of childbearing potential should be monitored for possible pregnancy using a urine dipstick test, which is performed at the trial site as described in the chapter 7.1.1. Additional hCG serum tests may also be performed at the local laboratory at the discretion of the investigator. See section 7.6.7 for further details on reporting pregnancies occurring during the study.

Pregnancies (of the patient or, if the patient is male, of the patient's partner) should be followed to determine the outcome (including spontaneous miscarriage, voluntary abortion, normal birth, or congenital abnormalities) and the status of both mother and child, even if the patient has been prematurely excluded from the study.

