| Eligibility for entering the long-term extension observational period: | 
 
1. Participation in the DARALUP core study
 
2. Written consent to the long-term extension observational period
 
3. In case of female patients of childbearing potential: she agrees to comply with effective contraceptive measures, has been using contraception since the last menses, will use adequate contraception during the study and has a negative pregnancy test at entering the LTE observational period
 
                                                                                                                                                                                                                                                                                                                                                                                                                                                                                                                                                                                                                                                                                                                                                                                                                                                                                                                                                                                                                                                                                                                                                                                     |

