13. all women of childbearing potential (WOCBP) must have a negative highly sensitive serum (beta-human chorionic gonadotropin [betahCG]) test at screening and a negative urine pregnancy test prior to first dose of study agent. Also, they must use a sufficient method of contraception (see section 5.3 PROHIBITIONS AND RESTRICTIONS).
14. a male participant must wear a condom with spermicidal foam/gel/film/cream/suppository when engaging in any activity that allows for passage of ejaculate to another person and must agree not to donate sperm for the purpose of reproduction during the study and for a minimum of 20 weeks after receiving the last dose of study intervention.
15. willing and able to adhere to the lifestyle restrictions specified in this protocol.

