## 5.4 PROHIBITIONS AND RESTRICTIONS

Potential subjects must be willing and able to adhere to the following prohibitions and restrictions to be eligible for participation:

- refer to Section 6.6 PROHIBITED THERAPY for additional details regarding therapies that are prohibited and restricted during the study.
- agree to follow all requirements that must be followed during the study as described in the Inclusion and Exclusion Criteria, Sections 5.1. and 5.2 (e.g. contraceptive requirements).
- agree to avoid excess exposure to natural or artificial (e.g. tanning beds, phototherapy) sunlight. In addition, it is advised that subjects maintain their typical use of sun protective measures (such as a hat, sunglasses, protective clothing, sunscreen). The time period for this requirement is from the start of screening until the last dose of study agent has been received.
- use of additional immunosuppressants or immunomodulators, other than those explicitly allowed in the inclusion/exclusion criteria (Section 5.1 and 5.2), are prohibited including but not limited to those listed in Section 6.9.
- must agree not to receive a live virus or live bacterial vaccination during the study.
- subjects must also agree not to receive BCG vaccination for 12 months after last dose of study agent, or any other live vaccine for 16 weeks after receiving the last administration of study agent.
- must agree not to receive an investigational medical device or an investigational drug other than study agent for the duration of this study.
- Skin concealers or topical tan preparations or nonpermanent tattoos should be avoided.
- within 48 hours before a study visit due to their potential to obscure skin disease activity.
- subjects should avoid use of any wigs or hair attachments that cannot be readily removed for scalp examination.
- Women of child bearing potential (WOCBP) must use a sufficient contraception during the time of study treatment, and 20 weeks thereafter. If the subject withdraws from the study prematurely, the 20 weeks must also be guaranteed.

Highly effective methods of contraception include:

- combined (estrogen and progestogen containing) hormonal contraception associated with inhibition of ovulation:
  - oral
  - intravaginal
  - transdermal
- progestogen-only hormonal contraception associated with inhibition of ovulation:
  - oral
  - injectable
  - implantable
- intrauterine device (IUD)
- intrauterine hormone-releasing system (IUS)
- bilateral tubal occlusion

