| SLE Serology for SLEDAI-2K (dsDNA abs, C3, C4)                      | X | X | X              | X              | X              | X              | X              | X              | X              | X              | X              | X              | X              | X              | X              |
| SLE Serology extended (ANA, ENA, Antiphospholipid antibodies, ACPA) | X | X | X**            | X**            | X**            | X**            | X**            | X**            | X**            | X**            | X**            | X**            | X**            | X**            | X**            |
| Serum vaccine titer                                                 |   | X | X              | X              | X              | X              | X              | X              | X              | X              | X              | X              | X              | X              | X              |
| Serum pregnancy test                                                | X |   |                |                |                |                |                |                |                |                |                |                |                |                |                |
| Urine pregnancy test                                                |   | X |                |                |                |                |                |                |                |                |                |                |                |                |                |
| Coagulation                                                         | X | X | X              | X              | X              | X              | X              | X              | X              | X              | X              | X              | X              | X              | X              |
| Antiglobulin Test                                                   |   | X | X # | X # | X # | X # | X # | X # | X # | X # | X # | X # | X # | X # | X # |
| Pharmacokinetics                                                    |   |   |                |                |                |                |                |                |                |                |                |                |                |                |                |

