## 7.6 SAFETY EVALUATIONS

Safety evaluations during this study include the assessment of AEs, concomitant drugs, pregnancy tests, injection related reactions (IRR), chemical and hematological laboratory tests, immunogenicity, vital signs and physical examinations. If the visit is on-site, a rapid SARS-CoV-2 test will be performed at each study visit. If this result is positive, a PCR SARS-CoV-2 test must follow for confirmation. In addition, screening procedures will include an electrocardiogram (ECG), chest x-ray (in accordance with local regulations), HIV testing, hepatitis B, hepatitis C and TB tests. All AEs and any clinically relevant changes in concomitant diseases occurring during the study must be recorded on the AE section of the CRF. The study will include the following evaluations of safety and tolerability at specific time points, as shown in the flow chart in section 7.1.1.

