### 7.7 SAMPLE COLLECTION AND HANDLING

Safety laboratory samples according to section 7.6.3 and all primary and secondary endpoints lab parameters will be analyzed in the local laboratory "LaborBerlin" and the handling is in accordance with clinical routine. The actual dates and times of sample collection should be recorded in the source data and CRF. Refer to section 7.1.1 for the timing and frequency of all sample collections.

The blood samples for the additional endpoint analysis according to chapter 7.5 will be analyzed at the laboratory of the Deutsches Rheuma-Forschungszentrum (DRFZ), located at the same campus as the Sponsor of this study. Instructions for the collection, handling, storage, and shipment of these samples are found in the laboratory manual. Collection, handling, storage, and shipment of samples should be under the specified, and where applicable, controlled temperature conditions as indicated in the laboratory manual.

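### Section 7.6.7 calls for pregnancy monitoring, but the plan as it reads schedules only entry tests: none is required during doses 2 to 8 or the 20 weeks after the last dose

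*Protocol*

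**What the plan says.** Section 7.6 counts pregnancy testing as part of safety follow-up: "Safety evaluations during this study include the assessment of AEs, concomitant drugs, pregnancy tests" and other items. Section 7.6.7 says that women who could become pregnant "should be monitored for possible pregnancy using a urine dipstick test, which is performed at the trial site as described in the chapter 7.1.1", and lets the investigator add serum hCG tests at discretion. Section 7.6.3 lists urine or serum pregnancy testing and sends the reader to the same flow chart for timing. Section 7.7 does likewise: "Refer to section 7.1.1 for the timing and frequency of all sample collections".

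In both copies of the core schedule, the row "Urine pregnancy test" carries one mark, at baseline, and the serum row carries one mark, at screening. The extension (LTE) schedule has one urine mark, in the Week 36 entry column.

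The text names tests only at points of entry. Inclusion criterion 13 in 5.1 asks for a serum test at screening and "a negative urine pregnancy test prior to first dose of study agent". The synopsis asks that a woman entering the extension "has a negative pregnancy test at entering the LTE observational period".

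Under 5.4, women of childbearing potential "must use a sufficient contraception during the time of study treatment, and 20 weeks thereafter". Sections 8.3 and 10.6 remove a patient who becomes pregnant, and 10.6 bars further study drug.

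**The concern.** Two tests before the first dose establish eligibility. They do not monitor anything. Section 7.6.7 promises monitoring but hands all timing to a schedule that, as it reads, stops at baseline, so a site that follows the protocol exactly runs no test while drug is being given after dose 1.

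The rule that stops treatment on pregnancy works only if a pregnancy is noticed. Without a scheduled test, that depends on the patient reporting it or on an investigator choosing to order hCG. What is at stake is avoidable exposure to later doses, and late recognition of a pregnancy within the period for which the protocol itself considers contraception necessary. No estimate or efficacy conclusion is affected.

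**Working it through.** The plan states no figure to reproduce. The check is a reading of the rows followed by calendar arithmetic on the schedule's own day row.

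**Inputs**
- Doses 1 to 8 on days 0, 7, 14, 21, 28, 35, 42 and 49 (core schedule; 6.2.1).
- Contraception for 20 weeks after treatment (5.4).
- Scheduled tests before Week 36, as the table reads: screening (serum) and day 0 (urine).
- Week 28 is day 189 (core schedule).

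**End of the contraception period**
49 + 20 × 7 = 49 + 140 = day 189, the Week 28 visit. Thirteen scheduled visits fall after baseline and up to day 189 (Weeks 2 to 9, then 12, 16, 20, 24 and 28). Seven of them are dosing visits. None has a pregnancy test in the row.

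**Days from last scheduled test to each dose**

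| Dose | 2 | 3 | 4 | 5 | 6 | 7 | 8 | Mean | Max |
|---|---|---|---|---|---|---|---|---|---|
| As the row reads | 7 | 14 | 21 | 28 | 35 | 42 | 49 | 196/7 = 28 | 49 |
| With a test before the Week 5 dose | 7 | 14 | 21 | 0 | 7 | 14 | 21 | 84/7 = 12 | 21 |

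Tests at Weeks 5, 9, 12, 16, 20, 24 and 28 fall on days 28, 56, 77, 105, 133, 161 and 189. The gaps, counted from day 0, are 28, 28, 21, 28, 28, 28 and 28 days, so none exceeds 28.

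**Doses given after a test would first be positive**
This is conditional on a pregnancy. It assumes that first positivity is uniform over the 49 dosing days, with no self-report and no discretionary test. By week of first positivity:
- As the row reads: 7, 6, 5, 4, 3, 2, 1; mean 28/7 = 4.0.
- With the added test: 3, 2, 1, 0, 3, 2, 1; mean 12/7 = 1.7.
- Difference: 4 doses if positive by day 28, otherwise 0; mean 16/7 = 2.3.

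**How often this would arise**
The protocol gives no contraceptive failure rate. As an assumption, take all 10 patients as women at risk and a failure rate of 1% to 5% per year.
- Dosing period: 10 × 49/365 × 0.01 to 0.05 = 0.013 to 0.067 pregnancies.
- To day 189: 10 × 189/365 × 0.01 to 0.05 = 0.05 to 0.26 pregnancies.
- Doses avoided in the whole trial: 0.013 to 0.067 × 2.3 = about 0.03 to 0.15.

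**Can the blank row be trusted?**
Only in part. The pages holding this row show 15 mark columns for 17 visits. The drug-concentration row is empty although 7.5 specifies Week 9. The ECG row is marked in the first two columns although 7.6.4 says screening and Week 36. These demonstrable errors are isolated marks. Rows with repeated marks survive on the same pages, some of them over-filled (the CLASI row is marked in every column). Loss of a whole series of on-treatment tests is therefore unlikely, while loss of a single Week 36 mark is plausible. For ECG and drug concentration the text supplies the missing visit. For pregnancy no text names any visit between the first dose and Week 36.

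**The case against.** The strongest objection is that the evidence is a blank in a damaged table. Agreement between the two copies of the core schedule adds little, because both also show the faulty ECG and drug-concentration rows. Criterion 13 and the extension criterion are eligibility rules and would not be expected to list on-treatment tests. This stands as a reason to read the source table before amending anything. It does not remove the point, because the text outside the table also requires no test in this period.

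A second objection is that nothing is contradicted: 7.6.7 sets no frequency, the schedule does contain urine tests, and a 4-weekly interval appears nowhere in the protocol. Other safeguards exist: exclusion of planned pregnancy, required contraception, two negative entry tests, a targeted examination before treatment, adverse-event review and discretionary hCG. All of this is fair. The point is a gap between the stated aim and what is scheduled, and the exact test grid is a preference.

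A reader might go further and infer that a woman who skips the extension is never tested again, that the untested gap runs all the way to Week 36, or that the early termination visit has no test even though 5.4 says "If the subject withdraws from the study prematurely, the 20 weeks must also be guaranteed". The documents do not support these readings. The extension's Week 36 entry column is the same visit as the end of the core study (visit 17), and an isolated core Week 36 mark may have been lost, as the ECG row shows. Nor is all dosing untested: a urine test precedes dose 1.

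**Conclusion.** The point holds in limited form. Nothing in the protocol as it reads requires a pregnancy test during doses 2 to 8 or in the 20 weeks after the last dose, although 7.6.7 speaks of monitoring and 10.6 makes further dosing depend on a patient not being pregnant. The interval from the last scheduled test to a dose reaches 49 days, and no test is scheduled after baseline up to day 189.

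This rests on the source table matching the extracted row. If on-treatment marks exist there, the point closes. The fall from 4.0 to 1.7 doses applies only if a pregnancy occurs and goes unreported. Under the assumed failure rates, well under one pregnancy is expected in the whole trial. This is therefore a worthwhile, inexpensive patient-safety improvement with no bearing on efficacy. No conclusion is drawn about the core Week 36 or early termination visits.

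**What to change.** 1. Check the pregnancy-test rows in the source document.
2. If they are as they read here, add a urine test for women of childbearing potential to both copies of the core schedule, about every 4 weeks at existing visits: at least before the Week 5 dose, at Week 9, and then through Week 28. One workable grid is Weeks 5, 9, 12, 16, 20, 24 and 28. Urine for the protein/creatinine ratio is already due at all of these under 3.2.3.
3. In 7.6.7, allow a recorded home test when a visit from Week 16 to Week 28 is held remotely under 7.1. State that a positive result withholds the next dose pending serum hCG, and that 10.6 applies if it is confirmed.

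The cost is one row in two tables and two sentences, by amendment. With that grid it is at most 7 × 10 = 70 strips, and no extra visit. Up to 4 of the 7 tests could be home tests, which are less controlled. The main downside is an occasional false positive that pushes a dose outside its ±1 day window; since 6.2.4 does not make up skipped doses, serum hCG should be returned quickly. The change does not give a test before every dose: doses 2 to 4 still rely on the baseline test and doses 6 to 8 on the Week 5 test.

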### 7.7 SAMPLE COLLECTION AND HANDLING

Safety laboratory samples according to section 7.6.3 and all primary and secondary endpoints lab parameters will be analyzed in the local laboratory "LaborBerlin" and the handling is in accordance with clinical routine. The actual dates and times of sample collection should be recorded in the source data and CRF. Refer to section 7.1.1 for the timing and frequency of all sample collections.

The blood samples for the additional endpoint analysis according to chapter 7.5 will be analyzed at the laboratory of the Deutsches Rheuma-Forschungszentrum (DRFZ), located at the same campus as the Sponsor of this study. Instructions for the collection, handling, storage, and shipment of these samples are found in the laboratory manual. Collection, handling, storage, and shipment of samples should be under the specified, and where applicable, controlled temperature conditions as indicated in the laboratory manual.

## 8 SUBJECT COMPLETION / DISCONTINUATION OF STUDY TREATMENT / WITHDRAWAL FROM STUDY

### 8.1 STUDY COMPLETION

A participant will be considered to have completed the core-study if he or she has completed assessments through Week 36. A participant will be considered to have completed the LTE-observational period if the assessment has been completed through Week 84. The study will be terminated once the planned case number of n=10 is reached, and the last patient has completed the last visit.

### 8.2 DISCONTINUATION OF STUDY TREATMENT

A participant will not be withdrawn from the study if he or she has to discontinue study agent before the end of the treatment regimen.

A subject's study agent must be discontinued if:

- Inclusion or exclusion criteria violation was noted after the subject started study drug, when continuation of the study drug would place the subject at risk as determined by the Investigator
- the Investigator, sponsor, and/or medical monitor believes that for safety reasons or tolerability reasons (e.g. adverse event), or due to severe, unstable, or rapidly progressive SLE disease activity, it is in the best interest of the subject to discontinue study agent.
- The subject (or the subject's legally acceptable representative) withdraws consent for administration of study drug.
- the subject develops study agent hypersensitivity (e.g. anaphylaxis, angioedema) reaction that is reported as serious or severe.
- the participant develops a serious opportunistic infection or SARS-CoV-2 infection confirmed by positive PCR-test (the follow-up phase can be continued once quarantine/COVID-symptoms/SARS-CoV-2 PCR positivity have resolved).
- if a new immunomodulator that is permitted per-protocol is initiated, then a participant will be considered a treatment failure but will not need to be withdrawn from the study.
- Occurrence of serious adverse events which are not compatible with the further administration of the study drug.

It is recommended that follow-up visit should be continued although patients might have discontinued study drug or had temporarily halt of study drug.

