## 5.1 INCLUSION CRITERIA OF THE CORE STUDY PERIOD

Each potential participant must satisfy all the following criteria to be enrolled in the study:

1. diagnosis of SLE according to the 2019 EULAR/ACR Systemic Lupus Erythematosus classification criteria.
2. age between 18 and 60 years, inclusive, at consent.
3. have a body mass index (BMI) between 18 and 32 kg/m^2 (BMI = weight/height), inclusive, and a body weight of no less than 35 kg.
4. demonstrate moderate to severe disease based on SLEDAI-2K score  $\geq 6$  observed at screening
5. SLEDAI-2K  $\geq 4$  for clinical features (i.e. SLEDAI excluding laboratory results) at screening
6. have a positive anti-double stranded deoxyribonucleic acid (anti-dsDNA) test, as measured by enzyme-linked immunosorbent assay (ELISA) test.
7. Failure or lack of tolerability of at least 2 previous state-of-the-art immunosuppressive drugs/immunomodulatory drugs including antimalarials (does not account for glucocorticoids).
8. if using oral corticosteroids, must be receiving this medication for at least 4 weeks and on a stable dose equivalent to an average dose of  $<20$  mg of prednisone daily for at least 4 weeks prior to the first dose of study agent.
9. if using immunosuppressive drugs within the past 6 months, must not have exceeded the following dose levels: methotrexate 25 mg/week, azathioprine 2mg/kg/day, mycophenolate mofetil (MMF) 3g/day, or mycophenolic acid (MPA) 1440mg/day.
10. if using immunosuppressive drugs, must be using not more than 1 immunosuppressive drug (does not account for antimalarials and glucocorticoids) and not have used any additional immunosuppressive drug within the past 3 months prior to the first dose of study agent.
11. must have laboratory test results within the following parameters:
  - a. Hemoglobin  $\geq 8.0$  g/dL (SI:  $\geq 80$  g/L)
  - b. White Blood Cells  $\geq 3.0 \times 10^3/\mu\text{L}$  (SI:  $\geq 3.0$  GI/L)
  - c. Neutrophils  $\geq 1.5 \times 10^3/\mu\text{L}$  (SI:  $\geq 1.5$  GI/L)
  - d. Platelets  $\geq 100 \times 10^3/\mu\text{L}$  (SI:  $\geq 100$  GI/L)
  - e. Serum creatinine  $\leq 2.0$  mg/dL (SI:  $\leq 177$   $\mu\text{mol/L}$ )
  - f. aspartate aminotransferase (AST) and alanine aminotransferase (ALT) levels must be within 2 x ULN range
12. must sign an informed consent form (ICF), indicating that he or she understands the purpose of, and procedures required for, the study and is willing to participate in the study.

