#### 6.4.1 GLUCOCORTICOID THERAPY

The use of glucocorticoids for the indication SLE is allowed to a maximum of 20mg daily prednisolone (or equivalent) throughout the study. The glucocorticoid dosage must be stable from baseline until Week 12 (primary endpoint study visit). After Week 12 (primary endpoint visit), it is possible to reduce the glucocorticoid dosage if the disease activity allows tapering, according to the judgment of the treating physician.

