### 6.5 RESCUE MEDICATION

For the treatment of disease flares, defined according to the SLEDAI-flare index (SFI), administration of glucocorticoids is allowed up to a maximum dose of 100mg/day. In case of recurring flares or ongoing disease activity, defined as a state of not achieving low disease-activity (LLDAS), administration of additional disease-modifying drugs is allowed from Week 12 (primary endpoint visit) (except for medications listed in section 6.6 PROHIBITED THERAPIES).

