### 7.2.3 SELENA-SLEDAI FLARE INDEX

One key secondary objective is to assess the flare rate in daratumumab treated patients. The corresponding secondary endpoint of this study is the time to first severe flare as measured by the modified SELENA-SLEDAI SLE Flare Index (SFI) [68]. This index categorizes SLE flares as either “mild or moderate” or “severe” based on six variables:

- change in SLEDAI-2K score from most recent assessment to current,
- change in signs or symptoms of disease activity,
- change in prednisone (or equivalent) dose,
- use of new medication for disease activity or hospitalization,
- change in PGA score,
- hospitalization for SLE activity (severe flare only).

The modified SELENA-SLEDAI SFI requires that a patient who has a SLEDAI score  $>12$  is considered as having a severe flare only if they have one other component present. This modification was made

because participants entering the trial with high disease activity (i.e.  $\geq 11$ ) could too easily trigger a severe flare by minor increases in SLEDAI score.

Lupus flares should be treated primarily with medications listed in the section 6.5 RESCUE MEDICATION. Only in case of insufficient response to such therapies and presence of severe SLE organ manifestations, medications listed in section 6.6 PROHIBITED MEDICATION can be used. In this situation, the participant will be considered as treatment failure but will not need to be withdrawn from the study (see section 8.2 DISCONTINUATION OF STUDY TREATMENT). To ensure that the interpretability of SLE FLARE INDEX will not be impacted by prohibited medication, such patients will be included in the intention-to-treat analysis set (see section 9.3. ANALYSIS SETS), similar to patients with a dose interruption in case of adverse events.

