### 7.3.2 LUPUS LOW DISEASE ACTIVITY STATE

In this study the following version of LLDAS is used and is defined as meeting all the following conditions [80]:

Disease activity:

- SLEDAI-2K  $\leq 4$ , with no activity in major organ systems (renal, CNS, cardiopulmonary, Vasculitis, fever), and no hemolytic anemia, or gastrointestinal activity
- No new features of lupus disease activity compared with the previous assessment  
SELENA-SLEDAI PGA score of  $\leq 1$  on a 0-3 scale VAS.

Immunosuppressive medications:

- A current prednisone (or equivalent) dose of  $\leq 7.5$  mg daily
- Well-tolerated standard maintenance doses of permitted immunosuppressive drugs and approved biological agents.

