### 7.3.3 SLE RESPONDER INDEX (SRI-4)

The SRI-4 response is defined as  $\geq 4$ -point reduction from baseline in SLEDAI-2K score, no new BILAG A and no more than 1 new BILAG B domain score, and no worsening from baseline in the PGA ( $< 10\%$  worsening from baseline) [65]. For the endpoint analysis in this study, SRI-4 composite response is the proportion of subjects who achieve a SLEDAI-2K SRI-4 response at Week 3, 5, 7, 9, 12, 16, 20, 24, 28, 32, 36 of the core study period, and at Week 42, 48, 54, 60, 66, 72, 78 and 84 of the LTE observational period.

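### After Week 12, patients the protocol declares treatment failures can still count as SRI-4 responders, and after a permitted add-on drug also as LLDAS responders

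*Protocol*

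**What the plan says.** Two rules in the Protocol create a treatment-failure status.

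- Section 8.2: "if a new immunomodulator that is permitted per-protocol is initiated, then a participant will be considered a treatment failure". The patient is not withdrawn.
- Section 7.2.3, for severe organ manifestations that have not responded adequately to rescue therapy: "medications listed in section 6.6 PROHIBITED MEDICATION can be used. In this situation, the participant will be considered as treatment failure". Again the patient stays in the study, and is kept in the intention-to-treat set.

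Section 6.5 sets when permitted drugs may be added. Besides repeated flares, it names this case: "ongoing disease activity, defined as a state of not achieving low disease-activity (LLDAS), administration of additional disease-modifying drugs is allowed from Week 12".

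The two responder endpoints are defined without reference to that status.

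- Section 7.3.3 requires a SLEDAI-2K fall of at least 4 points, limits on new BILAG A and B scores, and no PGA worsening. It then fixes the analysis: "For the endpoint analysis in this study, SRI-4 composite response is the proportion of subjects who achieve a SLEDAI-2K SRI-4 response at Week 3", and at the further listed visits to Week 84.
- Section 7.3.2 (LLDAS) has a drug component, but it accepts "Well-tolerated standard maintenance doses of permitted immunosuppressive drugs and approved biological agents" and does not separate newly started drugs from background therapy. Section 3.2.3 reports LLDAS by visit to Week 84.

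Section 9.3 analyses primary and secondary outcomes in all enrolled patients.

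**The concern.** Dosing ends at Week 8 and there is no control arm. The synopsis and section 3.1.5 use SRI-4 and LLDAS attainment to describe the long-term efficacy of daratumumab given earlier in the core study. If a patient starts another drug for active lupus after Week 12 and then improves, the stated rules place that patient among the responders at later visits, although the protocol has already called the same patient a treatment failure. The late proportions would then mix lasting response to daratumumab with response to the added drug, and would tend to overstate durability.

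**Working it through.** No figure in the plan has to be reproduced for this point. The check follows one patient through the stated rules and then sizes the effect.

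**Step 1: when the failure label can arise.** Section 6.5 opens additional disease-modifying drugs only from Week 12, which is Day 77 in the section 7.1.1 schedule. The last planned dose is Day 49, and section 6.2.4 does not allow the treatment period to be extended. 77 − 49 = 28 days, so a permitted add-on starts at least four weeks after planned dosing has ended (visit windows aside). The 8.2 label can therefore apply in practice only from Week 12, although the sentence stands in a list of reasons to stop a drug that is by then no longer being given.

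**Step 2: what happens to the responder status.**

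| Rule | New permitted drug (8.2) | Prohibited drug (7.2.3) |
|---|---|---|
| SRI-4 (7.3.3) | no drug component; can be a responder | no drug component; can be a responder |
| LLDAS (7.3.2) | permitted drugs accepted; can be a responder | only permitted drugs accepted; not while on the drug |
| Main analysis set (9.3) | included | included |
| Missing-value rule (9.4) | not triggered if the patient attends | not triggered if the patient attends |

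**Step 3: whether another section changes the count.**

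- Section 9.1.6 summarises new SLE medication by visit and lists patients with increases. It is a separate display.
- Time to new treatment (3.2.3, 9.5.2) and the flare index (7.3.4, where a new systemic immunosuppressant is itself a severe flare) record the drug start as separate endpoints.
- The modified intention-to-treat analysis (9.3) excludes patients who discontinued study treatment, for example because of prohibited medication. It covers that route only in part, since a course already completed cannot be discontinued. It does not clearly cover a permitted drug started after dosing has ended. It is also an additional analysis.

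None of these alters the main by-visit SRI-4 or LLDAS numerator.

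**Step 4: size.** Visits come from sections 3.2.3 and 7.3.3.

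- To Week 12: Weeks 3, 5, 7, 9, 12 = 5 visits.
- Rest of the core study: Weeks 16, 20, 24, 28, 32, 36 = 6 visits.
- Extension: Weeks 42, 48, 54, 60, 66, 72, 78, 84 = 8 visits.
- Total 5 + 6 + 8 = 19. After Week 12: 6 + 8 = 14, and 14/19 = 74%.
- Planned n = 10 (section 4.1), so each reclassified patient shifts a proportion by 1/10 = 10 percentage points.

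Illustration, with assumed counts: suppose 6 of 10 meet the criteria at a late visit. Exact (Clopper–Pearson) 95% intervals are in brackets.

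| Declared failures among the 6 | As observed | Failures as non-response |
|---|---|---|
| 1 | 60% (26–88) | 50% (19–81) |
| 2 | 60% (26–88) | 40% (12–74) |
| 3 | 60% (26–88) | 30% (7–65) |

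**The case against.** The strongest reply is that this is ordinary SAP content. The protocol refers to a SAP, no sentence says that failures count as responders, and the failure label can be read as a direction to code non-response. That would settle the matter if the protocol had left the endpoint open. It has not: section 7.3.3 fixes the SRI-4 rule for this study's endpoint analysis, and applying it literally counts these patients as responders. A SAP could add the missing link, but it would be adding to a stated rule.

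A second reply is that as-observed counting fits the intention-to-treat principle, and that with 10 patients the medication listings let a reader see who received what. This stands in part. The as-observed result is legitimate and should stay, and the listings limit the risk of misreading. They do not produce the responder count that the failure label implies.

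Third, section 6.5 does not itself call an add-on a treatment failure, so applying the 8.2 label after Week 12 involves some interpretation. That is fair, but section 6.5 gives the label no earlier period in which to operate.

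Three stronger readings are tempting and not supported:

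- *A reader might infer that LLDAS is open equally after prohibited drugs.* Section 7.3.2 accepts only permitted drugs. The shorter wording in section 3.2.3 omits that word, but this is too little to carry the claim.
- *A reader might infer that responders will routinely receive add-ons.* Entry allows stable prednisone below 20 mg/day, section 6.4.1 holds it until Week 12, and LLDAS needs at most 7.5 mg/day, so some improved patients cannot be in LLDAS at Week 12. But section 6.5 permits an add-on without requiring one, and tapering is allowed after Week 12. This shows that the route exists, not how often it is used.
- *A reader might infer that the main results are inflated.* Permitted add-ons do not reach the primary endpoint or the Week 12 SRI-4, which is the responder result that section 9.5.2 names.

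**Conclusion.** The point holds for SRI-4 after either failure trigger, and for LLDAS after a permitted drug, at visits after Week 12. Each affected patient moves a by-visit proportion by 10 percentage points if all 10 are analysed. The total effect is unknown, because the protocol gives no expected number of failures; the 1-to-3 range in the illustration is an assumption. The conclusion rests on reading section 7.3.3 literally and on the 8.2 label applying to drugs added under section 6.5. The endpoints are secondary and descriptive, with no confirmatory test, so what is at stake is an overstated durability of response. This is a worthwhile, inexpensive improvement rather than a flaw in the trial's main result.

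**What to change.** - In sections 7.3.3 and 9.5.2, report by-visit SRI-4 and LLDAS after Week 12 in two ways side by side: as observed, and with all visits after the first new systemic immunosuppressant or immunomodulator for SLE, permitted or prohibited, counted as non-response.
- In section 8.2, move the treatment-failure sentence out of the list of reasons to stop study agent, so that it clearly applies after dosing has ended.

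The cost is a few sentences and one extra row per visit for two endpoints. No new data are needed, because the schedule records concomitant therapy at these visits. The downside is that late responder proportions may look less favourable, and the non-response version counts some improved patients as failures. That is why the as-observed version should stay beside it.
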